#### Frailty status

Comparison with other training studies will be possible by using the frailty phenotype [39] as a measure of frailty status as primary outcome. Additionally, we will assess the frailty index [52, 53], which is calculated as the ratio of the number of deficits present out of a total number of 40 deficits assessed, including previous diseases, disability, psychosocial risk factors as well as physical and cognitive impairments [53]. Thus, the frailty index consists of a continuous score between 0 and 1 with higher values representing more pronounced frailty and increased susceptibility to adverse health outcomes [53]. While some studies demonstrated that frailty scores obtained from the two measures are comparable [54, 55], others have suggested that the frailty index might discriminate better at the lower to middle end of the frailty continuum [56] and might be more sensitive to measure change after an intervention [57]. Therefore, we will use both measures in a complementary rather than comparative manner [58].

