**Fig. 1 Fig1:**
[figure not shown]
Expected flow of participants and study design

The inclusion criteria will be an age of 65 to 95 years and the presence of at least one of the five frailty phenotype criteria [39], i.e. self-reported unintentional weight loss of > 5 kg in the prior year, self-reported exhaustion, low level of physical activity specified in kcal/week, muscle weakness as measured by low grip strength using a Jamar hand dynamometer, and slowness by slowed gait speed over 4.57 m. According to the phenotype model, the presence of one or two criteria is considered as pre-frailty while the presence of three or more criteria is considered as frailty [39]. We will include pre-frail as well as frail persons to investigate neuroplasticity mechanisms across a broader range of age-related functional decline, as the pre-frail stage is considered to describe a condition at high risk of progression to frailty [40, 41] and may be more amenable to change. Exclusion criteria will be: acute bone fractures within the last 3 months, immobility, paralysis or confinement to bed; stroke or neurological disorders with major cognitive or physical impairments; dementia; myocardial infarction within the last 6 months; life-time prevalence of mental disorders such as schizophrenia and other psychotic disorders, bipolar disorder, obsessive-compulsive disorder, post-traumatic stress disorder, drug or alcohol addiction; current severe major depression or other acute axis 1 mental disorders; current intake of benzodiazepines or antipsychotics; vitamin B12-, folate- or thyroid-stimulating hormone deficiency. Specific exclusion criteria will be examined during the first visit and include: cognitive impairment defined as a Mini Mental State Examination (MMSE) score of ≤ 24; severe impairments in sensory abilities (i.e. visual acuity of < 0.1; mechanical detection threshold of > 512 mN; severe or profound hearing loss according to the WHO, defined as a mean hearing threshold of > 60 dB; severe tinnitus symptomatology).

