### Sample size

Previous studies in healthy older humans using sensory training have achieved promising results with medium effect sizes and sample sizes of 41 to 53 subjects [5, 32]. Given that our training includes a multimodal stimulation approach and focuses on motivational enhancement within a virtual training environment, we assume that in our participants the effect of the experimental training program would exceed a medium effect size. To estimate sample size, we use a repeated measures design with one between-factor with two groups and one within-factor with three assessment points [43]. Assuming a medium effect size of Cohen’s f = 0.25, 95% statistical power, a correlation of 0.50 between the dependent measurements, and a two-sided alpha error level of .05, we therefore would need 22 participants in each group. To account for a drop-out rate of about 25% during the training, we will include 30 subjects per group (60 in total).

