### Outcome measures and biological moderators

The assessments will be performed according to the structure depicted in Table 1.

**Table 1 Tab1:** Overview of outcomes, outcome measures, instruments and assessment time points

Outcomes	Outcome measures	Instruments	Assessment time points
**Personal information**	• Age, sex, education, clinical history, medication	• Self reports	• T0, T1, T2
**Frailty assessments**	• Frailty status (pre-frail, frail) • Frailty Index	• Frailty Phenotype • Frailty Index	• T0, T1, T2 • T0, T1, T2
**Brain plasticity in the sensorimotor and somatosensory system**	• Structural and functional parameters of cortical sensorimotor and somatosensory maps • MEP peak-to-peak amplitude and latency	• fMRI motor sequence task, fMRI somato-sensory mapping task • TMS at left primary motor cortex	• T0, T1 • T0, T1
**Biological markers of neuroplasticity**	• BDNF serum blood levels (ng/ml)	• Collection of blood samples	• T0, T1
**Sensorimotor performance**	• SPPB (total score) • CTSIB (total score) • PPT (means)	• SPPB • CTSIB • PPT	• T0, T1, T2 • T0, T1 • T0, T1, T2
**Sensory functioning**	• Visual acuity • Visual contrast sensitivity • Tactile grating thresholds • Fine-touch thresholds • Hearing thresholds	• FrACT • FrACT • JVP domes • Von-Frey filaments • Audiometer	• T0, T1, T2 • T0, T1, T2 • T0, T1, T2 • T0, T1 • T0, T1
**Cognitive testing**	• MMSE (total score) • Mental and motor response speed • Top-down attentional control • Visuospatial working memory capacity • Executive functioning	• MMSE • RTI • AST • SSP • IED	• T0, T1, T2 • T0, T1 • T0, T1, T2 • T0, T1 • T0, T1
**Functional level and quality of life**	• Functional level in frailty • Depression • Overall health status and quality of life • Functional capacity in everyday activities • Falls self-efficacy • Nutritional status	• FEFA • CES-D • SF-36, EQ-5D-5L • MKS • FES-I • MNA	• T0, T1, T2 • T0, T1 • T0, T1, T2 • T0, T1 • T0, T1, T2 • T0, T1

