### Data analysis and handling

We will use mixed repeated measures analyses of variance for each of the outcome variables in order to assess the effect of the training at baseline, after 60 days, and after 90 days, as well as to unveil differences between the two groups. Significant time-by-group interactions will be further examined using post-hoc tests. To evaluate changes through the interventions, pre-post effect sizes will be computed and compared across interventions. The problem of missing data will be handled using multiple imputation.

Data collected in this project will be recorded, stored and analyzed anonymously. A list assigning codes to names will be stored separately under high security standards. Analysis of the data will be of scientific purpose only.

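### The primary outcome is listed as a two-level status (pre-frail, frail), which fits neither the planned repeated measures ANOVA nor the 95% power calculation

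*Protocol article*

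**What the plan says.** Under Frailty status, the comparison with other training studies is to be made "by using the frailty phenotype [39] as a measure of frailty status as primary outcome". The frailty index, described there as continuous from 0 to 1, is an additional measure.

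Table 1 (Outcome measures and biological moderators) gives the phenotype's outcome measure as "Frailty status (pre-frail, frail" and schedules it at T0, T1 and T2.

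The eligibility text in Study population and recruitment requires "the presence of at least one of the five frailty phenotype criteria". It sets the cut-points: "the presence of one or two criteria is considered as pre-frailty while the presence of three or more criteria is considered as frailty". It names no category for zero criteria. The same text says "We will include pre-frail as well as frail persons to investigate neuroplasticity mechanisms across a broader range of age-related functional decline", and adds that the pre-frail stage may respond more readily.

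Data analysis and handling states: "We will use mixed repeated measures analyses of variance for each of the outcome variables". It names no method for a categorical outcome.

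Sample size states: "we use a repeated measures design with one between-factor with two groups and one within-factor with three assessment points". The inputs are: "Assuming a medium effect size of Cohen’s f = 0.25, 95% statistical power", a correlation of 0.50 and two-sided alpha of 0.05. The result is 22 per group, raised to 30 for about 25% drop-out. The section does not name the outcome to which the calculation applies. It takes its effect size from sensory training in healthy older people.

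**The concern.** Three parts of the plan describe three different things: a two-level status, a model for means, and a power figure for a continuous score.

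The trial hypothesises a reduction in frailty and deliberately enrols pre-frail people, partly because they may be easier to improve. On the scale in Table 1, those people start at the better of two levels and can only stay or worsen.

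If the analysis follows Table 1, the primary test could miss an effect of the size the trial was planned to detect. A null result would be read against a 95% power claim that belongs to another kind of variable.

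**Working it through.** **1. The plan's own figure.** Inputs from Sample size: f = 0.25, k = 2 groups, m = 3 assessments, ρ = 0.50, α = 0.05. For the time-by-group interaction, assuming sphericity:

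- Noncentrality λ = f²·N·m/(1 − ρ), with df1 = (k − 1)(m − 1) = 2 and df2 = (N − k)(m − 1).
- N = 44: λ = 0.0625 × 44 × 3 / 0.5 = 16.5, df2 = 84, power 95.6%.
- N = 42: λ = 15.75, df2 = 80, power 94.6%.
- So 44 in total, 22 per group. Drop-out: 22 / 0.75 = 29.3, rounded up to 30.

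The arithmetic is right. It presumes a continuous, roughly normal score.

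**2. What the two-level scale can register.** Entry is at 1 to 5 criteria and the cut is at 3. The possible one-criterion improvements are:

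| Change | Effect on status |
|---|---|
| 5 to 4 | none (frail) |
| 4 to 3 | none (frail) |
| 3 to 2 | frail to pre-frail |
| 2 to 1 | none (pre-frail) |
| 1 to 0 | no category listed |

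The share of one-criterion improvements that registers therefore equals the share of participants entering with exactly three criteria, if each participant improves by one. The protocol does not give this share. Four assumed baseline mixes (percent with 1, 2, 3, 4, 5 criteria) give: 35/35/20/7/3, 20%; 50/30/15/4/1, 15%; 20 each, 20%; 25/25/30/15/5, 30%.

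**3. Power of the planned test on the two-level status.** The effect that gives 95% on a continuous score was applied to a latent normal score (SD 1, ρ = 0.50). That score was cut so that a chosen share is frail at baseline, and the planned time-by-group ANOVA was run on the 0/1 result (20,000 simulated trials per scenario).

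An effect of f = 0.25 fixes the latent shift. For a difference that is absent at T0 and constant at T1 and T2, the centred profile is (−2/3, 1/3, 1/3), with mean square 2/9. Each group carries half, so the shift is 0.25 / √((2/9)/4) = 1.06 SD. The other two profiles were an effect at T2 only (1.06 SD) and a gradual effect (0.80 SD at T1, 1.20 SD at T2). Ranges below span the three profiles.

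| Assumed frail at baseline | 22 per group | 30 per group |
|---|---|---|
| 50% | 56–58% | 70–72% |
| 30% | 33–37% | 45–49% |
| 20% | 22–26% | 29–34% |
| 10% | 11–14% | 15–18% |

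At 22 per group the uncut score gave about 96% in the same runs, in line with step 1. The loss comes from the scale. With 10% frail, a 1.06 SD shift lowers the frail share to 1 − Φ(1.28 + 1.06), about 1%. With 22 per group that is 2.2 against 0.2 expected frail participants.

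**4. Type I error.** The same ANOVA on the two-level status with no effect (22 per group, ρ = 0.50, 10–50% frail, 4,000 runs) rejected in 4.8–5.5% of trials.

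**5. The same effect on a 0–5 count.** Cutting the latent score into six levels and running the ANOVA on the count gave about 80–88% power at 22 per group and 92–96% at 30, under assumed baseline distributions (35–48% frail in those that set the lower ends). The nearest rows in step 3, 30% and 50% frail, show 33–58% and 45–72%.

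**The case against.** The strongest reply is that the two-level label is only a parenthesis in an overview table and may describe who is enrolled, since nobody enters with zero criteria. The instrument is a set of five criteria assessed at all three visits, and a 0–5 score is never ruled out. If a count was meant, the consequence is much smaller, as step 5 shows. This stands to the extent that the severity turns on which variable was intended. But the article never states a count. Its remark about scores from the two frailty measures describes cited studies. Adding an implied robust category would let 1 to 0 register, but not 2 to 1 or 5 to 3, and three ordered categories still do not match an f-based calculation.

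A second reply is that an unseen analysis plan may settle the model. The article, however, applies ANOVA to every outcome and states a power figure, so the mismatch lies in what it says.

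Several stronger readings are not supported:

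- **That ANOVA on a two-level outcome makes the test invalid.** In the scenarios of step 4, type I error stayed near 5%.
- **That most improvement is bound to go unseen.** This depends on a baseline mix that the protocol does not give.
- **That comparing two proportions at day 90 shows the trial's power.** That is not the planned test: it ignores baseline and the repeated measures, and its proportions are not tied to f = 0.25.
- **That the sample size was miscalculated.** It reproduces.

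**Conclusion.** The concern holds in this form: the primary variable, as listed, does not fit the planned model or the sample size calculation, and the 95% power does not apply to it. That a pre-frail entrant cannot improve on the listed scale, and that zero criteria has no category, follow from the definitions alone, provided Table 1's two levels are exhaustive at follow-up.

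The size is scenario-based: roughly 11–58% power at 22 per group and 15–72% if all 30 per group are retained. These ranges assume 10–50% frail at baseline, a latent normal score and an f = 0.25 interaction. The damage is reduced sensitivity and a power statement that would mislead anyone interpreting a null result. Because it affects the primary test, it should be corrected before the data are analysed.

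**What to change.** - **Frailty status and Table 1:** define the primary variable as the number of phenotype criteria present, 0–5, with 0 meaning robust. Report the three-level status (robust, pre-frail, frail) as supportive.
- **Data analysis and handling:** exempt the primary outcome from the blanket ANOVA and name a model suited to an ordered count and adjusted for the baseline count. Proportional odds is one example; other ordinal or repeated-measures models would also serve.
- **Sample size:** say that the 95% refers to a continuous measure, and restate power for the count. The figures of about 80–88% at 22 per group and 92–96% at 30 are for ANOVA on the count. They should be recomputed for the chosen model and a stated baseline mix, since a sample crowded at one criterion would give less.
- **Alternative:** make the continuous frailty index primary, with justification, and keep the existing calculation. This changes the primary measure, so it is the larger step.

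The cost is revised wording, a new power statement and, under the article's own commitment on important changes, an update to the trial registration. The criteria are already assessed at T0, T1 and T2, so no new data are needed. The downside is a less favourable stated power.

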#### Brain plasticity in the sensorimotor and somatosensory system

In order to track correlates of functional and maladaptive neural plasticity, we will measure neural processing and cortical representations in the sensorimotor as well as somatosensory system using functional magnetic resonance imaging (MRI).

Sensorimotor brain activation will be investigated using a motor sequence task encompassing three different motor exercises of varying complexity [59]. During each trial, participants will have to perform a sequence of button presses with their right hand using an MRI-compatible keyboard with five keys that are numbered from 1 to 5 and correspond to the thumb, index finger, middle finger, ring finger, and little finger, respectively. The task consists of three different exercises requiring repetitive tapping of a certain sequence: the “FINGER” condition consists of repetitive tapping of key no. 2 with the index finger, the “SIMPLE” condition consists of the sequence 1–2–3-4-5, and the “COMPLEX” condition consists of the sequence 1–3–5-2-4. The task will be carried out in a block-wise manner consisting of alternating movement and rest blocks.

Functional MR scans will be recorded using a 3 T Magnetom Trio system (Siemens, Erlangen, Germany) and a 32-channel head coil. Using an EPI gradient echo sequence, we will collect 40 slices with 2.3 mm slice thickness, TE = 22 ms, TR = 2100 ms, FoV = 220 × 220 mm^2^, voxel resolution = 2.3 × 2.3 × 2.3 mm^3^.

To investigate neuronal reorganization in the somatosensory system, we will perform a spatial mapping of the finger representations in the primary somatosensory cortex (S1) using two different protocols of somatosensory stimulation. Stimuli will consist of pneumatic sensations of touch automatically applied at a frequency of 1 Hz through a custom-made pneumatic device [60]. In a first run, tactile stimuli to the five finger pads will be separately applied in a random block design interspersed with rest blocks. In a second run, we will apply a well validated phase-encoding paradigm in which fingers will be continuously stimulated with no rest blocks. This approach has been demonstrated to reveal highly reproducible maps of individual digits in S1 [61]. Stimulation will cycle through blocks of fingers in an ascending and descending order. For both somatosensory paradigms, we will use an EPI gradient echo sequence and collect 22 slices with 1.8 mm slice thickness, TE = 22 ms, TR = 1500 ms, FoV = 220 × 220 mm^2^, voxel resolution = 1.2 × 1.2 × 1.8 mm^3^. In addition, we will acquire T1-weighted structural scans (TE = 2.72 ms, TR = 1900 ms, FoV = 250 × 250 mm^2^, voxel resolution = 0.8 × 0.8 × 0.8 mm^3^) to perform voxel-based morphometry.

#### Neuronal efficiency in the sensorimotor brain system

Age-related decline in sensorimotor performance has been linked to decreased neuronal efficiency in the sensorimotor system with respect to reduced motor cortex excitability [62, 63]. To investigate motor cortex excitability at baseline and after the intervention, we will perform single-pulse transcranial magnetic stimulation (TMS) at the left primary motor cortex (M1) and simultaneous recording of motor-evoked potentials (MEP) at the right abductor pollicis brevis. As measures of motor cortex excitability, we will calculate MEP peak-to-peak amplitudes and latencies. Prior to the stimulation, we will determine individual resting motor threshold (RMT), defined as the stimulation intensity at which at least 6 out of 10 MEPs reached a peak-to-peak amplitude of ≥50 μV [64]. We will then conduct three stimulation runs at 100, 110 and 120% of the RMT intensity in pseudorandomized order. Each run will consist of 20 consecutive stimulations with an inter-stimulus interval of approximately 10 s.

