We hypothesize that the sensorimotor training will have superior effects on frailty status compared with the control training, as reflected by a pre-to-post reduction in frailty indices and an improvement in frailty-related everyday functioning. On the neuronal level, we expect a refinement of sensorimotor representation maps and an increase in neuronal efficiency in the brain. Furthermore, we expect that such neuroplastic changes will be mirrored by a pre-to-post increase in BDNF serum levels. In addition, we will compare frailty-associated outcomes between BDNF genotypes that were shown to differ in terms of both BDNF secretion and the magnitude of training-related improvement [27, 38]. In the sensorimotor domain, we expect an increase in movement speed as well as an improvement in lower extremity motor function such as balance, and upper extremity motor function such as dexterity. With regard to sensory abilities, we expect an increase in visual, tactile, and auditory performance scores. Lastly, we expect the sensorimotor training approach to enhance psychological wellbeing, as reflected by an increased perceived health status and quality of life.

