## Methods

### Design

This randomized controlled trial will compare a tablet-based sensorimotor training (experimental group) and a tablet-based relaxation training (control group) in subjects suffering from frailty. Both conditions are conceptualized as a 90-day home-based intervention. Assessments will take place (1) before (baseline), (2) after 60 days (assessment 1) and (3) at the end of training (90 days; assessment 2) at the Institute of Cognitive and Clinical Neuroscience, Central Institute of Mental Health, Mannheim.

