### Procedure

Subjects fulfilling the general eligibility criteria as determined through the pre-screening will be invited for baseline assessments. During the first visit at the CIMH, subjects will provide written consent for participation. Specific eligibility criteria will be examined by a trained psychologist and a trained psychiatrist specialized in geriatric psychiatry. Individuals fulfilling the diagnostic criteria will then undergo behavioral, neuropsychological, and neurophysiological assessments conducted by the psychologist, and a physical and neuropsychological examination as well as the assessment of the medical history and medication conducted by the psychiatrist. Blood samples will be collected and conserved for analysis of BDNF serum levels and genotypes. After baseline assessments, subjects will be introduced to the respective training procedure by a psychologist. Support during the home-based treatment is also provided. After 60 and 90 days, the assessment of sensorimotor, neurocognitive and neurophysiological functioning will be repeated at the CIMH. Neuropsychological and physical examination including collection of blood samples will be repeated after 60 days. Prior to and after the training, participants will be asked for treatment expectation and evaluation, respectively, using five questions adapted from [42] to uncover motivational and affective aspects of the training. Subjects will not be paid for participation, but will be compensated for their travel costs.

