### Interventions

#### Experimental condition

The interactive tablet-based sensorimotor intervention will consist of three consecutive training phases with each phase comprising 30 days (90 days in total). The first phase will consist of unimodal sensory discrimination tasks in the visual, auditory and tactile domain to increase distinctiveness and acuity of cortical sensory representations. In the second phase, subjects will be trained on bimodal sensory integration using visual-auditory, visual-tactile and auditory-tactile tasks. Bimodal sensory integration will require subjects to process stimuli of two different perceptual modalities and judge whether the two stimuli are synchronous or not. These tasks are assumed to increase temporal acuity for multisensory integration and to promote plasticity in perceptual integration brain networks [44, 45]. Unimodal and bimodal stimuli are presented through the tablet involving explicit answers on the tablet’s touch screen. The third phase will require participants to process bimodal sensory information in order to control a sensorimotor response, in the form of visual-auditory guided cycling, visual-tactile determined grasping, and auditory-visual controlled hands coordination. In these sensorimotor integration tasks, sensory input must be interpreted and integrated in terms of the current state of the motor system to continuously adjust motor commands and behavior [46]. These tasks aim at improving motor acuity, i.e. to increase precision and reduce variability of motor performance by increasing the signal-to-noise ratio in sensorimotor brain networks [47, 48]. For tactile, cycling, and grasping tasks, we will use external devices that are wirelessly connected to and controlled by the tablet (i.e. a Braille display device for tactile tasks, a customized ergometer for cycling tasks, and a handgrip dynamometer for grasping tasks).

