*AST* Attention Switching Task, *BDNF* Brain-derived neurotrophic factor, *CES-D* Center for Epidemiologic Studies Depression Scale, *CTSIB* Clinical Test of Sensory Integration of Balance, *EQ-5D-5L* EuroQol-5D-5L, *FEFA* Frail Elderly Functional Assessment, *FES-I* Falls Efficacy Scale – International Version, *fMRI* Functional magnetic resonance imaging, *FrACT* Freiburg Vision Test, *IED* Intra-Extra Dimensional Set Shift, *MEP* Motor-evoked potential, *MKS* Marburg Competency Scale (Marburger Kompetenz Skala), *MMSE* Mini Mental State Examination, *MNA* Mini Nutritional Assessment, *PPT* Purdue Pegboard Test, *RTI* Reaction Time, *SF-36* Short Form-36 Health Survey, *SPPB* Short Physical Performance Battery, *SSP* Spatial Span, *T0* Baseline assessment, *T1* Assessment 1 after 60 days, *T2* Assessment 2 after 90 days, *TMS* Transcranial magnetic stimulation

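### Table 1 last measures fMRI, TMS and serum BDNF at day 60 of 90, before the sensorimotor phase, but the text calls this after the intervention (TMS) and pre-to-post (BDNF) and conflicts on when neurophysiology is repeated

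*Protocol article*

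**What the plan says.** All references are to the Protocol article.

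- **Length and phases.** The Design section states: "Both conditions are conceptualized as a 90-day home-based intervention". The Experimental condition section divides this into three consecutive 30-day phases: unimodal sensory discrimination, then bimodal sensory integration, then sensorimotor tasks. On the last it says: "The third phase will require participants to process bimodal sensory information in order to control a sensorimotor response".
- **Schedule.** The Table 1 row for brain plasticity lists "fMRI motor sequence task, fMRI somato-sensory mapping task" and TMS, each at T0 and T1. The BDNF row also has T0 and T1. The legend defines T1 as "Assessment 1 after 60 days"; T2 is day 90.
- **TMS text.** The section on neuronal efficiency begins its plan with "To investigate motor cortex excitability at baseline and after the intervention".
- **BDNF hypothesis.** The Objectives expect neuroplastic change to be "mirrored by a pre-to-post increase in BDNF serum levels".
- **Procedure.** "After 60 and 90 days, the assessment of sensorimotor, neurocognitive and neurophysiological functioning will be repeated at the CIMH". The next sentence places the repeat blood sample after 60 days and mentions no later one.
- **Analysis.** Data analysis and handling plans a mixed repeated measures analysis of variance for every outcome, to assess the "effect of the training at baseline, after 60 days, and after 90 days".

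**The concern.** The trial's rationale is mechanistic. Sensorimotor stimulation should refine cortical maps and raise neuronal efficiency, and those changes should accompany less frailty. If the last brain and BDNF measurements precede the phase in which participants cycle, grasp and coordinate their hands, a day-60 value is a mid-training value. Labelled as after the intervention or as pre-to-post, it would be reported as the result of a programme that participants had not finished. A null result for primary motor cortex excitability or for the motor-sequence task could then be taken as evidence against the sensorimotor training, although that training had not begun.

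There is also a practical problem. From the Procedure and Table 1 together, staff cannot tell whether fMRI and TMS are due at day 90, and the analyst cannot tell which model applies to the measures without a day-90 value.

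**Working it through.** The check is mainly one of timing, so the passages are set side by side.

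**1. Assessments placed on the phase calendar** (Experimental condition; Table 1 and legend)

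| Days | Training content | Assessment at end |
|---|---|---|
| 1–30 | Unimodal visual, auditory, tactile discrimination | none |
| 31–60 | Bimodal integration (synchrony judgements) | T1 |
| 61–90 | Cycling, grasping, hand coordination under sensory guidance | T2 |

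In the first two phases the answers are given on the touch screen. At T1, 60/90 = 67% of the training days have passed, including both sensory phases and 0 of the 30 sensorimotor days.

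**2. Statements on timing, by marker**

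| Marker | Table 1 | Procedure | Other text |
|---|---|---|---|
| TMS | T0, T1 | days 60 and 90 (as neurophysiology) | baseline and after the intervention |
| fMRI | T0, T1 | days 60 and 90 (if counted as neurophysiology) | refined sensorimotor maps expected, no day given |
| Serum BDNF | T0, T1 | day 60 | pre-to-post increase |

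The protocol does not define neurophysiological functioning. I assume that it means TMS and fMRI, the only Table 1 measures that the word fits. For these the Procedure contradicts Table 1. For BDNF the Procedure and Table 1 agree on day 60, so no passage provides a value at the end of training.

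**3. What a T0–T1 comparison estimates.** Both arms are randomised and both are measured at T0 and T1. The contrast therefore estimates the effect of 60 days of sensory training against 60 days of relaxation training. It contains no information on days 61 to 90.

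**4. Table 1 measures without a day-90 value.** Personal information is left out, the fMRI tasks count once, visual acuity and contrast sensitivity count separately, and so do SF-36 and EQ-5D-5L.

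- With T2 (13): frailty phenotype, frailty index, SPPB, PPT, visual acuity, contrast sensitivity, tactile grating, MMSE, AST, FEFA, SF-36, EQ-5D-5L, FES-I.
- Without T2 (12): fMRI, TMS, BDNF, CTSIB, von Frey filaments, audiometry, RTI, SSP, IED, CES-D, MKS, MNA.

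13 + 12 = 25. A model with three time levels cannot be fitted to the 12. The planned multiple imputation is no remedy, because it cannot properly supply a visit at which nobody is measured.

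**The case against.** Much of the case on the other side stands.

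- **A reader might infer that the mechanistic hypotheses go untested.** The documents do not support this. Phase 1 is meant to sharpen cortical sensory representations and includes tactile training on a Braille display. The somatosensory mapping task measures finger representations, which matches that training. BDNF is described as a marker of synaptic plasticity, not of motor training. The randomised day-60 contrast is a real test of the sensory phases.
- **A reader might infer that the link from brain markers to frailty is lost.** Table 1 measures both frailty instruments at T0, T1 and T2. Marker change to day 60 can be related to frailty change over the same interval, and to later frailty change. The link is limited, not lost.
- **A reader might take day 60 as settled for fMRI and TMS.** It is settled for BDNF only. For fMRI and TMS the demonstrable defect is a contradiction.
- **A reader might call the two-visit markers underpowered.** For the group-by-time interaction, λ = f²·N·m/(1 − ρ). With f = 0.25, N = 44, m = 3 and ρ = 0.50, λ = 16.5 and power is 0.956, which reproduces the plan's 22 per group. With m = 2, λ = 11 and power is 0.90. This is no defect: the Sample size section does not claim 95% power for these markers, and the 44 allows for drop-out over the whole training. With all 60 measured, power is 0.97.
- **The analysis sentence may be only a summary.** A mixed analysis of variance can be run with two time levels, and such detail may sit in an analysis plan. But the sentence as written names three time points for every outcome, and Table 1 does not provide them.

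**Conclusion.** The point holds as a matter of timing, wording and consistency. Under Table 1, fMRI, TMS and BDNF are last measured at day 60, after two of three phases and before any sensorimotor task. Against that schedule, the description of the TMS follow-up and the pre-to-post wording for BDNF are wrong, and the Procedure contradicts Table 1 on neurophysiology. The markers can show a 60-day effect of sensory training but not the effect of the 90-day programme or of its sensorimotor phase. The limitation is most serious for motor cortex excitability and the motor-sequence task, and least for the somatosensory maps. The three-time-point analysis does not fit 12 of 25 measures.

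For fMRI and TMS this rests on Table 1 being the schedule in force; if the Procedure is right and they are repeated at day 90, the error lies in Table 1 instead. For BDNF there is no such doubt. The frailty phenotype, the primary outcome, is measured at all three visits and is unaffected.

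**What to change.** 1. Make the Procedure, Table 1 and the TMS section agree on when fMRI and TMS are done.
2. For every marker measured only at T0 and T1, word the hypothesis as the effect of the first 60 days (the sensory phases) and remove the after-intervention and pre-to-post wording. State that a null motor result does not bear on the sensorimotor phase.
3. Analyse these outcomes as day-60 values adjusted for baseline, compared between arms. Limit the three-time-point analysis of variance to outcomes measured at T0, T1 and T2.

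These are changes of text and model specification. They need no further scan or blood draw. The cost is a narrower claim: the mechanism of the complete programme is not assessed by these markers.

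Moving the single follow-up of fMRI, TMS and BDNF to day 90 is possible only for participants not yet assessed. It adds no procedure, but it creates two subcohorts with different follow-up days, gives up the readout of the sensory phases in the later one, and exposes the measurement to later drop-out. It is an option to weigh, not a necessary part of the repair.
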